### Data management

Anonymised outcome and healthcare resource use data will be received from Optimum Patient Care (routine primary care data), the Healthcare-Learning eLearning module database (training data), questionnaires and transcripts of focus groups and interviews. These will be uploaded onto a central study database stored on the servers based at University of East Anglia (UEA). The database will be password protected and only accessible to members of the ARRISA-UK trial team at NCTU, external regulators and process evaluation teams. The server is in a secure room, which is protected by closed-circuit television, where access is restricted to members of the UEA Information Systems team by security door access. The study database has been built using Microsoft Structured Query Language (SQL) Server tools and all Internet traffic is encrypted via an Hypertext Transfer Protocol Secure (HTTPS) connection, using Transport Layer Security (TLS) v1.2 and RSA 4096.u. periodically and at database lock the data will be checked for errors and inconsistencies. The database is designed to comply with the principles of the International Conference on Harmonisation (ICH) Good Clinical Practice (GCP), within the Standard Operating Procedures (SOP) for Data Management in NCTU and also where appropriate with UEA IT procedures. The database and coding values have been developed by the Head of Data Management in conjunction with the study statistician and other NCTU members.

### Sample size

A total sample size of 8204 patients from 235 practices will provide 90% power to detect a difference in the primary outcome (asthma crisis events) from 7% to 5% (effect size of 0.3) assuming a cluster size of 35 and intraclass correlation coefficient (ICC) of 0.01. These estimates are from the event rate and prevalence of predicted hospitalisations and A&E attendance, as a whole and per practice, obtained from a database of 48,000 patients obtained from Optimum Patient Care, and the cluster size and ICC from our regional trial [22]. The average cluster size was estimated from CRNs. Patients will, as noted above, only be removed from the register in exceptional circumstances and we estimate that less than 10% of patients will leave their practice [31]. Therefore, we planned to evaluate a total of approximately 9170 patients with at-risk asthma from 262 practices. However, the initial average cluster size (39 patients per cluster) was greater than estimated and we propose to increase the sample size to 270 practices with 10,530 patients. If more than 10% of practices do not undergo minimum training and flagging, additional practices will be recruited. A decision to stop the study will be considered if the power of the study is reduced to less than 80% or when more than 30% of practices fail to undergo training to a minimal degree and/or do not activate the flag.

### Randomisation

Practices will be randomised to the intervention or control, in a 1:1 ratio, based on a computer-generated randomisation code, prepared by the study statistician, with stratification for practice software (Vision/EMIS/SystmOne) and presence of an asthma-diploma-trained nurse at the practice (yes/no) at randomisation. Emails are sent to practice managers and practice champions informing them of their allocation with appropriate log-in details for the study website and, for the intervention practice, the eLearning modules.

### Blinding

This pragmatic cluster randomised controlled trial is being conducted with blind assessment and analysis of outcomes. The practices (clusters) cannot be blind to the intervention. The patients with asthma may or not be blind to the intervention depending on whether individual practices decide to inform patients they are on an ‘at-risk’ register. As far as possible, those researchers not interacting with the practice sites will remain blind throughout the study and analysis. The statistical analysis team will be blind to the intervention throughout. The health economists will be blind during their initial determination of costs and until that point in the analysis plan where they must include costs associated with the allocation. The researchers implementing the intervention, including the primary care physician leading the webinar training programme, the qualitative interview and focus group researchers and the research trial staff providing assistance on practice sign up, follow-up phone calls and providing support for the software, are, of necessity, aware of allocation.

### Analysis

#### Effectiveness analyses

The primary comparison of treatment arms at 12 months will be based on the intention-to-treat (ITT) principle including all patients initially identified with ‘at-risk’ asthma using the risk algorithm. The primary outcome will be analysed on an individual-level using a logistic regression model with random effects to allow for the clustering of patients by practice and fixed effect for the factors included in the stratification, i.e. practice software and practice diploma-trained nurse. A similar model will be used for the number of events, based on a Poisson regression model with random and fixed effects, and the time until the first event. Secondary outcomes will be analysed in a similar fashion, which is to say that the binary outcomes will be analysed using logistic regression models and all count outcomes using Poisson regression. All model assumptions will be assessed using appropriate techniques and for Poisson regression models over dispersion will also be checked.

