### Intervention

This is a practice-wide (cluster-level) complex intervention comprising four main components:

1. Establishment of a practice at-risk asthma register:

We have developed and validated an algorithm, using routinely collected primary care data, for identifying those patients most at risk of attending A&E, being admitted to hospital or dying from an asthma attack. Factors in the algorithm include previous exacerbation history, coding for anxiety or depression, smoking history and prescribing data and laboratory results. Automated electronic searches identify patients with at-risk asthma from practice-based data using this algorithm. This is a two-stage process with the initial generation of an anonymised list and then coding to provide the names and details of the patients. Programmes and instructions for searches, with frequently asked questions, for the specific computer software programme of each practice will be sent to the information technology (IT) lead at the practice by email or compact disc (CD).

A representative (usually asthma GP lead or asthma nurse) at each intervention practice receives a document by email which explains ‘at-risk asthma’ and gives instructions on how to modify the list of patients with their records flagged (see CDSS below). GPs and asthma nurses are able to review the computer-generated list of at-risk patients, and exceptionally, with documented justification of the change, delete any who should not be on the list (e.g. receiving palliative care) and identify any other ‘at-risk’ patients known to them. They may modify the list, as above, for the duration of the study although the primary analysis will be based on data from patients included in the original register prior to modifications

2.  Practice-wide, online training (eLearning)

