### Data collection

#### Baseline characteristics and outcome data

All practices expressing interest in the study are asked to complete an initial questionnaire to provide basic data on practice characteristics.

All participating practices must agree to share their practice EHRs with Optimum Patient Care (Cambridge, UK). Obtaining data in this way not only permits linkage to different databases (practice EHRs, Office for National Statistics (ONS), Hospital Episode Statistics (HES)), but also permits data capture without burdening the practice or patients. All practices (control and intervention) are asked to insert a specific Read code that cannot be readily removed by practice staff into the EHRs of at-risk asthma patients to denote inclusion in this study. This will be used by data managers and statisticians to identify these patients and distinguish their data from other patients with active asthma in the practice. For the purposes of data collection, active asthma is defined using the QOF criterion [27]: Read code for asthma diagnosis plus asthma therapy in the past year, excluding those coded as asthma resolved but not excluding QOF exception codes. At the end of the study, data extractions will be obtained for all patients with asthma in the practice containing data for the 12 months before randomisation and the 12 months following the activation of the flag in the intervention practices. The mean time from randomisation to activation of the flag will be calculated for all intervention practices, and data collection will be captured for 12 months from this time after randomisation in the control practices. For clinical event data and for patients’ demographic and other characteristics (weight, height, smoking status, etc.) the last recorded value will be obtained.

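### The primary model adjusts only for the two stratification factors and leaves out prior-year crisis events that the extract should already supply; the model is valid, but a modest gain in power is forgone

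*Protocol article*

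**What the plan says.** Under Effectiveness analyses, the primary outcome (any asthma-related crisis event over 12 months) is analysed at patient level by logistic regression with a practice random effect and "fixed effect for the factors included in the stratification, i.e. practice software and practice diploma-trained nurse". No further covariate is named. Neither that section nor Additional subgroup analyses gives the pre-randomisation year any role.

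Under Baseline characteristics and outcome data, the extract is described as "containing data for the 12 months before randomisation" as well as the follow-up year, with linkage to hospital and mortality records. Prior crisis events are not listed as a baseline variable, but they should be derivable from such an extract.

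Under Intervention, the risk algorithm is meant to find the patients most likely to attend A&E, be admitted or die from an asthma attack. "Factors in the algorithm include previous exacerbation history", alongside mental-health coding, smoking, prescribing and laboratory data.

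Under Sample size, "A total sample size of 8204 patients from 235 practices will provide 90% power" for 7% against 5%, "assuming a cluster size of 35 and intraclass correlation coefficient (ICC) of 0.01". No allowance is made for covariate adjustment.

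**The concern.** A patient's crisis history in the year before randomisation cannot be affected by allocation. It is the baseline counterpart of the primary outcome, and the trial treats a closely related quantity as a predictor of that outcome. Adjusting for it would protect against chance imbalance between arms, which the two stratification factors do not address directly, and would add some power. If prior events also track stable differences between practices, adjustment would absorb part of the between-practice variance behind the design effect. The choice has to be made in advance, because adding the term after results are seen would be open to challenge.

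**Working it through.** **1. The plan's own figure.** Inputs from Sample size: 7% v 5%, 90% power, cluster size 35, ICC 0.01. Randomisation gives 1:1 allocation. The article does not state alpha; two-sided 0.05 is assumed.

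- Two-proportion formula: n = [1.96√(2×0.06×0.94) + 1.2816√(0.07×0.93 + 0.05×0.95)]² / 0.02² = 2961.02, rounded up to 2962 per arm.
- With continuity correction: 3060.2, rounded up to 3061 per arm.
- Design effect: 1 + 34×0.01 = 1.34.
- Total: 2×3061×1.34 = 8203.5, i.e. 8204. Then 8203.5/35 = 234.4, i.e. 235 practices.

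Both stated figures reproduce exactly, with no covariate gain used.

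**2. Unadjusted reference.** Log odds ratio = ln[(0.05/0.95)/(0.07/0.93)] = −0.358 (OR 0.699). Variance per patient = 1/(0.5×0.07×0.93) + 1/(0.5×0.05×0.95) = 72.8. SE = √(72.8×1.34/8204) = 0.1091. So z = 3.280, and power = Φ(3.280 − 1.96) = 90.7% (no continuity correction).

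**3. Patient-level term added.** Let q be the share of register patients with a prior-year crisis event and ψ its odds ratio for a new one. The documents give neither, so both are assumptions. The intercept and treatment effect are solved so that the overall risks stay at 7% and 5%. The variance comes from the inverse information matrix of the logistic model with treatment and prior event, with the same design effect. Relative efficiency is (z adjusted / z unadjusted)².

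| q | ψ | Conditional log OR | SE | z | Relative efficiency | Power at 8204 |
|---|---|---|---|---|---|---|
| 20% | 2.5 | −0.362 | 0.1097 | 3.299 | 1.011 | 91.0% |
| 20% | 4 | −0.369 | 0.1107 | 3.330 | 1.030 | 91.5% |
| 10% | 5 | −0.370 | 0.1110 | 3.337 | 1.035 | 91.6% |

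The extreme corners of the 10–20%, OR 2.5–5 range give 1.008 (10%, OR 2.5; power 90.9%) and 1.043 (20%, OR 5; power 91.8%). A wider range, q 5–20% and ψ 2–10, gives 1.002 to 1.10.

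The SE rises by about 0.6–1.7% in the three scenarios (0.1097–0.1110 against 0.1091). The gain arises because the conditional log odds ratio moves away from zero by more than that.

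**4. Between-practice variance.** If adjustment also halved the ICC to 0.005 (an assumption), the design effect would be 1 + 34×0.005 = 1.17. Effective patients per arm would rise from 4102/1.34 = 3061 to 4102/1.17 = 3506, and power by the two-proportion formula from 90.9% to 94.1%. Simulations of the three scenarios that assumed a between-year practice correlation of 0.7 gave relative efficiencies of about 1.04–1.11 for the patient term and 1.04–1.14 with the practice's prior-year rate added. The documents support no value for that correlation.

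**5. At the raised target.** With 270 practices, 39 patients each and 10,530 patients, the design effect is 1 + 38×0.01 = 1.38. Unadjusted power is 95.6% before attrition. With the patient term it is 95.7–96.3% across the 10–20%, OR 2.5–5 range.

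**6. Chance imbalance.** Take q = 10% and ψ = 5. Control risks are 22.0% with and 5.3% without a prior event. A 1.96-SD imbalance in q between arms of 4102 is 1.96√(2×0.1×0.9/4102) = 1.30 percentage points, which shifts the crude difference by 0.0130×(0.220 − 0.053) = 0.22 points. Across the range the shift is about 0.10–0.24 points, or 5–12% of the 2-point target. This ignores clustering of prior events, which would widen it.

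**The case against.** The strongest reply is that nothing here is wrong. The model matches the design, gives a valid test and does not need the covariate to reach its stated power. All of that stands.

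A second reply is that an unseen analysis plan could add baseline covariates. This carries less weight: the article describes the primary model's fixed effects specifically and does not leave the set open, so a longer list would depart from the published model.

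A third reply concerns strength, and it also stands. The algorithm uses exacerbation history, which is not the same as a prior A&E attendance or admission. No odds ratio or ranking of predictors is given. Everyone in the primary analysis was selected by that algorithm, so the spread and prognostic value of event history on the register may be reduced.

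A reader might infer that substantial precision is being thrown away, or that the strongest known predictor has been omitted. The documents do not support either. They give no strength for any predictor, and the confidence interval for the log odds ratio would not narrow. Gains of 7–12% in effective sample size can be obtained, but they rest on an assumed practice-level correlation between years or on odds ratios well above 5.

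**Conclusion.** The point holds as a low-cost improvement. The primary model makes no use of pre-randomisation crisis events that the extract should already contain, so modest power and protection against chance imbalance are forgone. Assuming 10–20% prevalence and an odds ratio of 2.5–5, the patient-level term is worth about 1–4% in effective sample size, or less than about one percentage point of power at 8204 patients. Any larger benefit depends on how far prior events explain between-practice variance, which cannot be judged from the documents. Confidence is high in what the text says and low in the exact size. The validity of the primary analysis and the stated 8204 patients in 235 practices are not in question.

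**What to change.** Before any outcome data are seen:

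- Add to the primary model, as a pre-specified fixed effect, whether the patient had an asthma-related crisis event in the year before randomisation (yes/no). Optionally add the practice's prior-year crisis proportion among register patients. Keep the practice random effect and both stratification factors.
- Use the matching prior-year count in the event-rate model.
- State whether the reported odds ratio is conditional or marginal, because adding the covariate changes the conditional quantity slightly (0.690 against 0.699 at 10% prevalence and OR 5).
- Set a simple rule for patients without a full prior year of records, for example coding the events observed and adding an indicator for an incomplete year.
- Report the current model as a sensitivity analysis.

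The cost is a few sentences in the analysis section and one derived variable. No new data collection should be needed, and the sample size does not change.

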#### Secondary outcomes

The time to first, and rate of, asthma-related crisis event(s) (defined as above) for at-risk patientsThe percentage of all registered asthma patients with an asthma-related crisis event, their rate of, and time to, first asthma-related crisis event(s) (as above)The percentage of at-risk and all registered asthma patients with good control defined as answering ‘no’ to all of the RCP3Qs [29]The percentage of at-risk and all registered asthma patients requiring a hospital admission or dying for any reasonThe number of the following (per patient per year) for both at-risk and all registered asthma patients:

(a) short-acting bronchodilator prescriptions issued

(b) prescriptions of systemic corticosteroids for asthma attacks and antibiotic-treated lower respiratory tract infections

(c) modifications of the prescription of asthma-related medications to align more closely with current guidelines (e.g. increased use of inhaled corticosteroids)

(d) records of written personalised asthma action plans and patient self-monitoring with peak flow diaries

(e) inhaler technique assessments recorded

(f) smoking cessation advice or smoking cessation medications given

(g) flu vaccinations

(h) ‘did not attends’ at primary and secondary care routine appointments

(i) adherence to medication determined from validated computer-based calculations using prescription data

Health economic outcomes6.The estimated (per patient) mean incremental cost of the at-risk register compared with usual care7.The incremental effect of the at-risk register, in terms of the estimated (per patient) mean difference (between arms) in the number of asthma crisis events

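### Flu vaccination is listed as a count and so falls to Poisson regression, which makes its test in at-risk patients conservative when uptake is high and the practice ICC is low

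*Protocol article*

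**What the plan says.** The Secondary outcomes section of the Protocol article gives some outcomes as percentages of patients: crisis event, good control, and admission or death for any reason. A separate block of nine items, (a) to (i), is introduced as numbers per patient per year, for at-risk patients and for all registered asthma patients. That block contains "g) flu vaccinations" and "i) adherence to medication determined from validated computer-based calculations using prescription data".

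The Effectiveness analyses section assigns models by type of outcome: "binary outcomes will be analysed using logistic regression models and all count outcomes using Poisson regression". The count model is described as "based on a Poisson regression model with random and fixed effects", and secondary outcomes follow the same pattern. On checking, it says: "All model assumptions will be assessed using appropriate techniques and for Poisson regression models over dispersion will also be checked".

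**The concern.** The article separates percentages from numbers and places flu vaccination with the numbers. Read with the analysis section, that gives it a Poisson model. Over a 12-month window a flu vaccination is essentially yes/no, and for such an outcome the Poisson variance is too large. A practice random effect can add variance to the model but cannot take it away. The one dispersion check that is named looks in the other direction: "for Poisson regression models over dispersion will also be checked".

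The Aims section names vaccinations among the processes of care to be examined, and the process evaluation uses process-of-care outcomes to explain how the intervention works. If the standard error is too wide, a real improvement in vaccination could be reported as no change, with a confidence interval that is also too wide.

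There is a lesser point on adherence. It is derived from prescription-data calculations and is unlikely to be a count, so the list of numbers is the wrong place for it.

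**Working it through.** **Inputs from the article (Sample size and Randomisation sections).** Planned cluster size m = 35; ICC = 0.01, given for asthma crisis events; 7% against 5%; 90% power; 1:1 allocation. The later observed mean cluster size is 39, with 270 practices.

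**Assumed, because the article does not give them.** Two-sided 5% test; at most one vaccination per patient in the window; uptake p from 50% to 80%; vaccination ICC from 0.01 to 0.05.

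**Step 1: reproduce the plan's own figure.** Two proportions, 7% against 5%, two-sided 5%, 90% power, with continuity correction: 3061 per arm. Design effect 1 + (35 − 1) × 0.01 = 1.34. Total 2 × 3061 × 1.34 = 8203.5, which matches "A total sample size of 8204 patients from 235 practices will provide 90% power". The design-effect formula used below is therefore consistent with the plan's own calculation.

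**Step 2: compare the variances.** Treatment is constant within a practice, so the practice total carries the information.
- True variance of a yes/no total: m·p(1−p)·[1+(m−1)ICC].
- Poisson variance without a random effect: m·p.
- Ratio: r = (1−p)[1+(m−1)ICC].

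If r is 1 or more, the random effect absorbs the excess and the test is about right. If r is below 1, the random-effect variance goes to zero and the Poisson standard error is too large by a factor 1/√r.

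**Step 3: convert to error rate and power.** The effective critical value is 1.96/√r. For an effect that the correct model detects with 90% power, Poisson power is Φ(3.24 − 1.96/√r), where 3.24 = 1.96 + 1.28.

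Worked case, p = 0.7, m = 35, ICC 0.01: r = 0.3 × 1.34 = 0.402; 1/√r = 1.58; critical value 3.09; power Φ(3.24 − 3.09) = 0.56; actual type I error 0.2%.

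Poisson power when the correct model has 90% (m = 35):

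| ICC | design effect | p = 0.5 | p = 0.6 | p = 0.7 | p = 0.8 |
|---|---|---|---|---|---|
| 0.01 | 1.34 | 80% | 71% | 56% | 29% |
| 0.03 | 2.02 | 90% | 86% | 77% | 56% |
| 0.05 | 2.70 | 90% | 90% | 86% | 72% |

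At ICC 0.01 the actual size of the nominal 5% test is about 1.7%, 0.7%, 0.2% and 0.02% across the four uptakes.

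**Step 4: where the problem ends.** r reaches 1 when p = 1 − 1/[1+(m−1)ICC]. For m = 35 this is about 25% uptake at ICC 0.01, 50% at 0.03, 63% at 0.05 and 77% at 0.10. Below those uptakes nothing is lost.

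**Step 5: check by simulation.** Beta-binomial data were generated for 270 practices of 39, with the effect set for 80% power and 400 data sets per setting. Each was fitted with random-intercept Poisson and random-intercept logistic models. Simulation error is about 2 points for power.

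| ICC | p | Poisson | logistic |
|---|---|---|---|
| 0.01 | 0.5 | 64% | 80% |
| 0.01 | 0.6 | 54% | 77% |
| 0.01 | 0.7 | 43% | 81% |
| 0.03 | 0.5 | 80% | 81% |
| 0.03 | 0.6 | 72% | 79% |
| 0.03 | 0.7 | 60% | 81% |

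Simulated Poisson type I error at ICC 0.01 was 1.8%, 0.5% and 0.0%. At ICC 0.05 with 60% uptake the two models differed by less than 1 point. The pattern agrees with the closed form.

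**The case against.** **The routing is inferred.** The analysis section assigns models by data type, so if vaccination is binary it could be said to have the logistic model already. The heading over the list is also loose, since adherence is not a number of anything. This has some force, but the article puts its percentage outcomes elsewhere and words them as percentages. On its face 5(g) is a count. At the least, the two sections leave the choice open to whoever codes the variable.

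**Vaccination might not be strictly 0 or 1.** Windows start at flag activation, practice by practice, so one window could hold a late dose from one season and an early dose from the next. That stands as a caveat; such cases should be few.

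**The general check of assumptions could catch it.** It could. However, no fallback model is named, and the only specific dispersion check is for excess variance.

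**The consequence is limited.** This is one item of a nine-part secondary outcome on which the trial is not powered, and the error is conservative. All of that stands.

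**Stronger readings that the article does not support.**
- A reader might infer that the test always under-rejects. It does so only when (1−p)(1+(m−1)ICC) is below 1.
- A reader might infer that 20 or more points of power are lost. With m = 39 and 80% nominal power, that needs uptake above about 57% at ICC 0.01, 66% at 0.02, 72% at 0.03 and 80% at 0.05. Neither uptake nor a vaccination ICC is given, and the 0.01 belongs to crisis events.
- A reader might infer that Poisson variance is also too large for adherence. The article describes only "adherence to medication determined from validated computer-based calculations using prescription data" and gives no scale. With an assumed mean of 0.7, SD of 0.2 to 0.3, m = 39 and ICC 0.01, the ratio of true to Poisson variance is 0.08 to 0.18 on a 0–1 scale but about 8 to 18 on a 0–100 scale. The direction reverses, so nothing can be said about direction or size.

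**Conclusion.** The point holds in a conditional form. As written, flu vaccination is a count and is analysed by random-effects Poisson regression, which overstates the variance of a yes/no outcome. In at-risk patients the test is conservative when uptake is high relative to the practice-level clustering. At the article's cluster size of 35 and its crisis-event ICC of 0.01, a test that should have 90% power has about 80%, 71% and 56% at uptake of 50%, 60% and 70%. The loss disappears at 50% uptake with ICC 0.03, or at 60% uptake with ICC 0.05. In the all-asthma population the clusters are larger, so the loss is smaller.

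These figures rest on one vaccination at most per patient and on assumed uptake and ICC. For adherence, all that can be said is that it is unlikely to be a count and is misplaced in the list; a fuller analysis plan may already name its model. The primary analysis is unaffected. The change is worth making because it costs almost nothing, not because the trial's main conclusion is at risk.

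**What to change.** In Secondary outcomes, redefine 5(g) as the percentage of patients with a flu vaccination recorded in the 12-month window. In Effectiveness analyses, state that it is analysed with the logistic random-effects model already specified for binary outcomes, with the stratification factors as fixed effects. This also settles any window that happens to hold two doses.

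Take adherence, 5(i), out of the list of numbers, state its scale, and name a model that suits it, for example a linear mixed model with a practice random effect if it is continuous. Keep Poisson regression for events that can recur, such as prescriptions.

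This is a wording change in two places, with no new data and no extra patients. For vaccination the only cost is that the effect is reported as an odds ratio rather than a rate ratio.
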